### Eligibility criteria

Patients eligible for the trial must comply with all of the following at randomisation:

#### Inclusion criteria

➢ Patients diagnosed with limited cutaneous systemic sclerosis according to the 2013 ACR/EULAR criteria experiencing RP➢ Men or women aged 18–80 years old➢ Disease duration between 1 and 10 years➢ Patients should be able to perform exercise

#### Exclusion criteria

➢ Patients with advanced pulmonary arterial hypertension or interstitial lung disease➢ Patients diagnosed with another inflammatory condition➢ Patients presenting myositis with proximal muscle weakness➢ Patients with New York Heart Association class 3 or 4➢ Current smokers or people who stopped smoking within 4 weeks of health screening➢ Women who are currently pregnant

#### Withdrawals

Patients will be considered as withdrawn from the research trial if they request to leave the trial, if they are lost to follow-up or if they die before completing the 6-month follow-up.

### Baseline measurements

At Visit 1, following the provision of written informed consent and the confirmation of eligibility (which will include a medical examination), the following baseline measurements will be recorded:Demographic data, including age, sex and socioeconomic statusClinical history, including incident or recurrent RP, duration of disease, duration of RP attacks, current medications, height, weight, body composition (percentage body fat and lean muscle mass)Baseline exercise historyHRQoL questionnaires: EQ-5D-5L [19] and RP diary and condition score [20]Cutaneous microvascular function using LDF combined with the iontophoresis technique in the reference finger [21, 22]Functional capacity using the 6-minute walking test [23]VO_2peak_ will be performed on an arm-crank ergometer

### Exercise intervention

The exercise group will undertake twice weekly supervised exercise sessions at the Centre of Sport and Exercise Science at Sheffield Hallam University for 12 weeks (total of 24 sessions). The weekly training structure and the training hours will be flexible to work around patients’ commitments, although sessions in two consecutive days will be avoided to allow sufficient recovery between sessions. The duration of the exercise intervention is based upon evidence reporting that an average training dose–response of 12 weeks significantly improves the macrovasculature in several disease states [12]. A maximum of 14 weeks will be allowed for the patients to complete the 24 sessions, to allow for missed sessions due to, for example, illness or holiday.

Each session will comprise of a 5-min warm-up period (involving light aerobic exercise and gentle range of motion exercises). This will be followed by an arm-cranking HIIT for 30 s at 100% of peak power output interspersed by 30 s passive recovery for a total of 30 min. The HIIT protocol will be combined with RT lasting for a total of 15 min. RT will consist of an upper body circuit training (five exercises) for three circuits. The intensity will be at 75–80% of one repetition maximum performing 10 repetitions of each exercise interspersed by 20–30 s to allow for safe movement between exercises. The recovery period between circuits will last 2–3 min. Following each exercise session, patients will undertake a 5 min cool-down period, involving upper-limb light intensity aerobic exercise and some light stretching. Patients will wear heart rate (HR) monitors throughout the exercise sessions. HR and the rating of perceived exertion (RPE) will be assessed at regular intervals throughout the supervised exercise session. The whole duration of each exercise session will be approximately 45 min.

### Clinical management

All the patients in both studies will continue receiving their standard medical treatment, i.e. calcium channel blockers (nifedipine, sildenafil), and will be reviewed in the clinic as often as is deemed clinically necessary. Moreover, in case of adverse events or worsening of symptoms due to exercise or patients request, patients will be withdrawn from the study for health and safety reasons.

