## Methods/Design

### Study design

The FESS (Feasibility of Exercise in Systemic Sclerosis patients) study is a mixed methods feasibility study involving a randomised controlled trial. Thirty patients with SSc receiving usual care (e.g. medical treatment) will be randomly assigned (via block randomisation remotely by the study chief investigator) to either an exercise group (12-week supervised exercise programme) or to a control group being in receipt only of the usual care. Patients will be followed for 6 months following randomisation (Fig. 1). It is not feasible to perform masking of patients or study investigators regarding the allocated treatments due to limited resources. The study is being run at Sheffield Hallam University in collaboration with the Royal Hallamshire Hospital (Sheffield Teaching Hospitals, NHS, UK). The study’s protocol and registration have been published in ClinicalTrials.gov (NCT number: NCT03058887).

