### Safety monitoring

We will record all serious adverse events (as defined below), as well as all non-serious adverse events that are deemed to be related to participation in the research, during the period between the provision of informed consent through to 6 months after randomisation.

Serious adverse events are defined as any untoward medical occurrence that either results in death, is life-threatening (i.e. the patient is at risk of death at the time of the event occurring), requires unplanned admissions to emergency hospitalisations or prolonged hospitalisation (deemed to be where a patient’s stay is longer than expected, e.g. patient is operated on as a day case but remains in hospital overnight), results in persistent or significant disability or incapacitation, or results in a congenital abnormality or birth defect.

A non-serious event in the context of this trial will be any untoward medical occurrence to the participant that is related to the patients’ involvement in the study but does not fulfill any of the serious adverse event criteria.

Study investigators will be responsible for recording adverse events and for determining the seriousness, severity, causality and expectedness of any such events. The Chief Investigator (MK) and a delegated clinician (MA) will then be responsible for reviewing all adverse events and confirming that they have been appropriately classified.

A serious adverse event will be reported to the Research Ethics Committee and Sponsor where, in the opinion of the Chief Investigator and the delegated clinician, the event was related to the administration of a research procedure or resulted in death regardless of relatedness.

Patients will be asked to contact the study team to inform them about adverse events if and when they occur. Study investigators will also question patients about the occurrence of adverse events during each participant study visit.

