### Outcome measures

The timeline for the outcome measures will be the baseline measurements, and the 3- and 6-month follow-ups after randomisation.

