### Feasibility outcomes

The primary aim of this study is acceptability and feasibility of procedures for recruitment, allocation, measurement and retention as well as the adherence and enjoyment levels of the exercise programme. Recruitment rates will be assessed as the rate of invited patients who are eligible and consenting and will be reported in a CONSORT (Consolidated Standards of Reporting Trials) patient flowchart. Suitability of measurement procedures will be assessed via interviews and reasons for missing data. Reasons for dropouts will be used to evaluate the acceptability of allocation procedures and exercise programme. The acceptability of the exercise programme will also be assessed through questionnaires relevant to exercise task self-efficacy, intentions for engagement to exercise, enjoyment levels of exercise and the affect during exercise, and the physiological stress of exercise monitored by HR and RPE. The safety of exercise will be evaluated by the dropout number from the exercise group, and the number and type of adverse events.

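### Patients harmed by the exercise are removed from the study rather than from training only, which costs their remaining follow-up visits and lowers retention, a primary outcome

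*Protocol article*

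**What the plan says.** Clinical management in the protocol article sets the rule: "in case of adverse events or worsening of symptoms due to exercise or patients request, patients will be withdrawn from the study". The sentence goes on to give health and safety as the reason. It names the study, not the exercise programme, and sets no severity threshold.

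The Withdrawals section counts a patient as withdrawn "if they request to leave the trial, if they are lost to follow-up or if they die before completing the 6-month follow-up". Removal by the team for an adverse event is not on that list.

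Elsewhere the article plans complete follow-up:

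- Study design: "Patients will be followed for 6 months following randomisation".
- Outcome measures: "The timeline for the outcome measures will be the baseline measurements, and the 3- and 6-month follow-ups after randomisation".
- Safety monitoring: adverse events are recorded "during the period between the provision of informed consent through to 6 months after randomisation", and "Study investigators will also question patients about the occurrence of adverse events during each participant study visit".

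Feasibility outcomes gives dropouts two uses: "Reasons for dropouts will be used to evaluate the acceptability of allocation procedures and exercise programme", and "The safety of exercise will be evaluated by the dropout number from the exercise group, and the number and type of adverse events". The Abstract lists retention among the primary outcomes, and the first objective in the Background is to estimate it for a definitive trial.

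**The concern.** Stopping a treatment and leaving a trial are different events, and the rule merges them. A patient who should stop arm-cranking for safety can usually still complete a quality-of-life questionnaire and answer questions about adverse events. Three things are at stake.

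- **Retention.** The estimate mixes patients' willingness to stay with removals that the protocol itself imposes. A definitive trial that kept such patients in follow-up would need the first without the second.
- **Safety and acceptability.** The patients affected by exercise lose the adverse-event questioning held at study visits. A patient removed before month 3 is also no longer a participant when the acceptability interviews take place.
- **Secondary comparisons.** Events due to exercise arise mainly in the exercise arm, in patients who have done badly. The missing measurements are then related to outcome and unequal between arms. The article gives no basis for determining the size of any resulting bias.

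**Working it through.** **Comparing the sections.** Take a patient who has an exercise-related adverse event in week 6 and is willing to stay. Under Clinical management this patient is withdrawn from the study. Under Withdrawals the patient is not withdrawn, having neither asked to leave, been lost, nor died. The schedules in Study design, Outcome measures and Safety monitoring would have the patient seen at 3 and 6 months. No section says that such a patient may stop training and remain in follow-up.

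**The plan's own figures.** The article states no expected retention and no adverse-event rate, so there is no such figure to reproduce. Its only precision statement (Statistical analysis) concerns the proportion willing to be randomised. At n = 30 the 90% half-width is 1.645 × √(0.35 × 0.65/30) = 14.3 points at 35%, and 14.7 points at 40%. This agrees with the stated 15 points and is not in dispute. It supplies the denominators used here: 15 per arm and 30 in total.

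**Cost of one removal from the exercise arm.**

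- Exercise-arm retention: 1/15 = 6.7 points.
- Overall retention: 1/30 = 3.3 points.
- Post-baseline assessments lost: 2 of 2 if removed before month 3, or 1 of 2 if after. Removal after month 3 is possible because Exercise intervention allows up to 14 weeks to complete the sessions.

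**Illustration.** Let k be the number of exercise-arm removals, with no other loss. The values of k are assumptions. Planned exercise-arm follow-up visits are 15 × 2 = 30.

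| | k = 1 | k = 2 | k = 3 |
|---|---|---|---|
| Exercise-arm retention, (15 − k)/15 | 93.3% | 86.7% | 80.0% |
| Overall retention, (30 − k)/30 | 96.7% | 93.3% | 90.0% |
| Visits lost, all removed before month 3, 2k/30 | 6.7% | 13.3% | 20.0% |
| Visits lost, all removed after month 3, k/30 | 3.3% | 6.7% | 10.0% |
| Shift in completer mean, d = 0.5 to 1 SD | 0.03–0.07 SD | 0.07–0.13 SD | 0.10–0.20 SD |
| Sample-size inflation, 30/(30 − k) | 3.4% | 7.1% | 11.1% |

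If the same patients had stopped training but kept their visits, retention would be 15/15 and 30/30 in every column.

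For the fifth row, let C be the completers' mean and R the mean the removed patients would have had. The full-arm mean is [(15 − k)C + kR]/15, so the completer mean differs from it by (k/15)(C − R) = (k/15)d. The range for d is also an assumption.

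The last row applies only if a planner divides by overall retention and ignores the reasons for dropout.

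**The case against.** The strongest reply is that the sentence is loosely drafted and means stopping the exercise. Taken literally it would remove a patient for any exercise-related event, however minor, which is hard to believe was intended. The Withdrawals list and the general schedules fit the looser reading. The article gives no retention formula, so counting these patients as not retained is an inference. General schedules are always subject to withdrawals, so the only direct inconsistency is between Withdrawals and Clinical management. That last point is accepted: the rule undercuts the schedules rather than contradicting them. The looser reading, however, requires the sentence to mean something other than what it says, and a patient withdrawn before month 6 cannot sensibly count as retained.

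Second, health and safety is a real motive, because the assessments include an arm-crank test to exhaustion and a 6-minute walk. This justifies omitting those tests. It does not justify ending questionnaires and adverse-event enquiry.

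Third, there are mitigations. Recorded dropout reasons would let a report split retention by cause. Clinic review and patient self-report remain as routes for safety information, and the Statistical analysis section mentions imputation. All of this stands and limits the harm, but none of it supplies measurements that were never taken.

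Fourth, the consequences are hypothetical and small next to the study's noise. The largest illustrated shift, 0.20 SD, is about half the standard error of a difference between two arms of 15, √(2/15) = 0.37 SD, and those comparisons are secondary. This is fair. The case rests mainly on the primary outcome and on safety follow-up.

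**Conclusion.** The concern holds. As written, the rule ends study participation for patients whose problem is with the exercise, and it is inconsistent with the Withdrawals definition. The firm part of the size is 6.7 points of exercise-arm retention, 3.3 points overall, and one or two lost assessments per removal. The number of removals and any bias in the secondary comparisons cannot be determined from the article; the figures for one to three removals and for 0.5 to 1 SD are illustrations.

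Two readings underlie this: that withdrawal from the study ends its remaining visits, and that a patient withdrawn before month 6 does not count as retained. Both follow the plain meaning of the text, but neither is spelled out. The point does not invalidate the study and is worth correcting because the remedy is cheap.

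**What to change.** - **Clinical management:** state that patients with adverse events or worsening due to exercise stop the exercise programme but, unless they withdraw consent, remain for the 3- and 6-month assessments, omitting any clinically unsafe test, and for adverse-event recording to 6 months.
- **Withdrawals:** state that stopping exercise is not withdrawal from the trial.
- **Data collection:** record stopping exercise, with date and reason, separately from leaving the study.
- **Reporting:** count stopping exercise under adherence, tolerability and the exercise-group dropout measure of safety. Count only leaving the study against retention. Report any patients already removed under the existing rule as such.

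When training must stop is a clinical decision and is left as it is.

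The cost is a protocol amendment and one form field. Patients who stop training would be seen at visits already planned. Trial status describes recruitment as ongoing, so later patients can benefit, but the change cannot recover data from anyone already removed.

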### Data management

The study will adhere to the Data Protection Act (1998). Data from this study will be anonymised and stored in password-protected computer systems accessible only by the members of the research team in order to guarantee confidentiality to patients. Paper forms will be stored in locked filing cabinets. All data documents will be kept in a secured and continuously monitored building where the project will be conducted ([name], Sheffield Hallam University). All study materials will remain in this location for data entry and storage. Double data entry will be implemented to ensure validity and data quality. Participant names will not be used to identify any data. Instead, patients will be assigned a study identification number in order to anonymise their information.

Data will all be anonymised according to the NHS Code of Confidentiality and GMC Good Medical Practice, while publications will not contain identifiable personal data. Furthermore, only research team members will have access to personal patient data during the project, while data will be analysed locally by the study’s statistician. Data will be kept for a 10-year period following the study completion to allow the study team to re-analyse it in case of the development of a new method of analysis and for the data to be used for the development of a future definitive RCT.

### Safety monitoring

We will record all serious adverse events (as defined below), as well as all non-serious adverse events that are deemed to be related to participation in the research, during the period between the provision of informed consent through to 6 months after randomisation.

Serious adverse events are defined as any untoward medical occurrence that either results in death, is life-threatening (i.e. the patient is at risk of death at the time of the event occurring), requires unplanned admissions to emergency hospitalisations or prolonged hospitalisation (deemed to be where a patient’s stay is longer than expected, e.g. patient is operated on as a day case but remains in hospital overnight), results in persistent or significant disability or incapacitation, or results in a congenital abnormality or birth defect.

A non-serious event in the context of this trial will be any untoward medical occurrence to the participant that is related to the patients’ involvement in the study but does not fulfill any of the serious adverse event criteria.

Study investigators will be responsible for recording adverse events and for determining the seriousness, severity, causality and expectedness of any such events. The Chief Investigator (MK) and a delegated clinician (MA) will then be responsible for reviewing all adverse events and confirming that they have been appropriately classified.

A serious adverse event will be reported to the Research Ethics Committee and Sponsor where, in the opinion of the Chief Investigator and the delegated clinician, the event was related to the administration of a research procedure or resulted in death regardless of relatedness.

Patients will be asked to contact the study team to inform them about adverse events if and when they occur. Study investigators will also question patients about the occurrence of adverse events during each participant study visit.

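### Non-serious adverse events are recorded only if unmasked investigators judge them related to the research, so their counts cannot support an unbiased comparison between arms

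*Protocol article*

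**What the plan says.** All references are to the protocol article.

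- **Safety monitoring, recording rule.** From consent to 6 months after randomisation, every serious adverse event is recorded. Non-serious events are limited to "all non-serious adverse events that are deemed to be related to participation in the research".
- **Safety monitoring, definition.** Relatedness appears again in the definition of a non-serious event: "any untoward medical occurrence to the participant that is related to the patients’ involvement in the study", where no seriousness criterion is met.
- **Safety monitoring, who judges.** Study investigators are responsible for "determining the seriousness, severity, causality and expectedness of any such events". The Chief Investigator and a delegated clinician then review the classification.
- **Safety monitoring, elicitation.** Patients are asked to report events as they happen. In addition, "Study investigators will also question patients about the occurrence of adverse events during each participant study visit".
- **Study design.** "It is not feasible to perform masking of patients or study investigators regarding the allocated treatments".
- **Outcome measures.** The shared assessment schedule is "the baseline measurements, and the 3- and 6-month follow-ups after randomisation".
- **Feasibility outcomes.** "The safety of exercise will be evaluated by the dropout number from the exercise group, and the number and type of adverse events".

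**The concern.** A randomised control arm shows how many events occur without the intervention, so that an excess can be seen without anyone having to attribute individual events. Here attribution comes first and decides which non-serious events exist in the data. The people attributing know the arm, and the arms differ in what an event can be attributed to: 12 weeks of supervised training plus the assessments in one, the assessments alone in the other.

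Two errors become possible. The same background complaint may be logged in an exerciser and passed over in a control patient, which creates an apparent excess. Alternatively, a complaint that exercise does aggravate may be put down to the disease and never logged, and there is no control rate to reveal the mistake.

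This is a rule about data capture. An analysis plan cannot recover events that were never written down. The Discussion says that the findings will inform a definitive multicentre trial, so the safety reading carries forward.

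**Working it through.** The plan gives no adverse event rate or safety target, so there is no figure of its own to reproduce. The check sets the sections side by side and then illustrates the mechanism on assumed inputs.

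**Step 1: what passes the filter in each arm**

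| Type of event | Exercise arm | Control arm |
|---|---|---|
| Serious, any cause | recorded | recorded |
| Digital ulcer, iloprost admission, amputation (reported under EQ-5D-5L questionnaire) | reported | reported |
| Non-serious, judged due to shared assessments (iontophoresis, arm-crank test, heated skin probe, walk test) | recorded | recorded |
| Non-serious, judged due to training | recorded | cannot arise |
| Non-serious, judged background | not recorded | not recorded |

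The rule reads the same for both arms. The imbalance arises because one complaint, such as shoulder pain, can fall in the fourth row or the fifth for an exerciser. For a control patient it falls in the fifth unless it is tied to an assessment.

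**Step 2: illustration**

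Formula: expected recorded events in an arm = patients × true events per patient × probability of being judged related.

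Inputs:
- 15 patients per arm (Statistical analysis).
- The same true rate in both arms, that is, no effect of exercise. Assumed: 1, 2 or 4 events per patient.
- Probability of being judged related. Assumed: 0.30 to 0.80 in the exercise arm and 0 to 0.20 in the control arm.

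| True events per patient | True events per arm | Recorded, exercise | Recorded, control |
|---|---|---|---|
| 1 | 15 × 1 = 15 | 15 × 0.30 = 4.5 to 15 × 0.80 = 12 | 0 to 15 × 0.20 = 3 |
| 2 | 15 × 2 = 30 | 30 × 0.30 = 9 to 30 × 0.80 = 24 | 0 to 30 × 0.20 = 6 |
| 4 | 15 × 4 = 60 | 60 × 0.30 = 18 to 60 × 0.80 = 48 | 0 to 60 × 0.20 = 12 |

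With full recording the two arms would show equal expected counts in every row. The direction follows from assuming that attribution is likelier in exercisers. The size is not an estimate for this trial.

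**Step 3: opportunities to be asked**

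Both arms have 3 assessments. If training sessions also count as study visits, exercisers have 24 + 3 = 27 occasions against 3. The article does not say whether they count, so this is conditional and the finding does not depend on it.

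**Step 4: what full recording could show with 15 per arm**

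Suppose 2 of 15 control patients have a given event (assumed). The two-sided Fisher exact p-value is 0.109 for 7 of 15 exercisers, 0.0502 for 8 of 15 and 0.021 for 9 of 15. Only an excess above fourfold (9 against 2) would reach the 5% level.

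**The case against.** The strongest defence is that the rule is explicit and consistent, and that much of the safety information lies outside it.

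- **The filter is relation to the research, not to exercise.** Control patients undergo finger iontophoresis, an exhaustive arm-crank test, a heated skin probe and a walk test, so their events can qualify. This stands. A reader might infer that the control arm will record almost no events; the article does not say so, and the rule leaves room for control events.
- **Other safety data remain.** Serious events and the digital outcomes are captured in both arms whatever their cause, related events in exercisers are logged, and reasons for dropout are collected. A Raynaud's diary and condition score is listed at baseline (its follow-up timing is not separately stated), and the 3-month interviews cover experiences of Raynaud's in six patients per arm. This also stands. A reader might infer that the safety of exercise cannot be judged at all; these sources show that it can in part.
- **The background section's figure of about 30% annual morbidity from digital ischaemia might seem to size the gap.** It does not. The Discussion ties that figure to hospitalisation and amputation, which are captured elsewhere.
- **No between-arm test of adverse events is planned, and 15 per arm could not support one.** This is correct and limits the gain to description. It does not remove the fault, because event counts are still a named basis for judging safety.
- **Senior review and dropout counts act as safeguards.** This is weaker. Review confirms the classification of recorded events, and a non-serious event judged unrelated falls outside the recording rule. The dropout measure named for safety covers the exercise group only. The Clinical management section also ties some withdrawals to worsening attributed to exercise, which is again an unmasked judgement.

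**Conclusion.** The point holds for non-serious adverse events only. As written, their counts cannot support an unbiased comparison between arms, because an unmasked relatedness judgement decides what is recorded and the arms differ in what an event can be related to.

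The size is unknown. The documents supply neither a background rate nor attribution probabilities, and the illustrated 9 to 24 against 0 to 6 recorded events, from 30 true events per arm, rests wholly on assumed values. The conclusion requires only that attribution differs between arms, which is likely when investigators know the allocation and one arm trains under supervision.

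This is a cheap improvement to a stated outcome, not a flaw that undermines the trial.

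**What to change.** Amend the Safety monitoring and Feasibility outcomes sections and the event form as follows:

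1. Record all non-serious adverse events in both arms regardless of relatedness, and take relatedness out of the definition.
2. Elicit them with the same standard question in both arms at the common 3- and 6-month visits, covering the time since the previous assessment.
3. Keep causality as a separate field, assessed after the event has been logged.
4. Tabulate these events by arm descriptively. List events noted during training sessions separately, so that closer contact does not inflate the comparison.
5. Show dropouts, with reasons, for both arms in the safety summary. The planned CONSORT flowchart and dropout reasons already supply most of this.

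The cost is a change of wording and a modest increase in events to log in 30 patients. The Trial status section says that recruitment is ongoing, so the change should start in both arms on the same date, with events before and after it distinguished. Patients will still know their allocation when they report, so the change removes the attribution filter but not all reporting bias.
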